## Abstract

The cerebellum (CB) has extensive connections with both cortical and subcortical areas of the brain, and is known to strongly influence function in areas it projects to. In particular, research using non-invasive brain stimulation (NIBS) has shown that CB projections to primary motor cortex (M1) are likely important for facilitating the learning of new motor skills, and that this process may involve modulation of late indirect (I) wave inputs in M1. However, the nature of this relationship remains unclear, particularly in regards to how CB influences the contribution of the I-wave circuits to neuroplastic changes in M1. Within the proposed research, we will therefore investigate how CB effects neuroplasticity of the I-wave generating circuits. This will be achieved by downregulating CB excitability while concurrently applying a neuroplastic intervention that specifically targets the I-wave circuitry. The outcomes of this study will provide valuable neurophysiological insight into key aspects of the motor network, and may inform the development of optimized interventions for modifying motor learning in a targeted way.

## Introduction

The ability to modify patterns of motor behaviour in response to sensory feedback represents a fundamental component of effective motor control. This process underpins our capacity to learn new types of motor skills, and to improve their performance with practice. While this error-based motor adaptation is a complex process involving a distributed brain network, extensive literature has shown that the cerebellum (CB) plays a critical role (for review, see; [1]). This structure is thought to facilitate generation and ongoing modification of internal models of neural activation that determine effector dynamics. These internal models are constantly updated based on comparisons between predicted and actual sensory feedback, allowing improved task performance with practice. As an extension of this process, communication between CB and primary motor cortex (M1) is crucial [2, 3], and may facilitate retention of the generated internal model [4]. However, the neurophysiological processes underpinning this communication remain unclear, largely due to the difficulty of assessing the associated pathways in human participants.

Despite this, non-invasive brain stimulation techniques (NIBS) such as transcranial magnetic stimulation (TMS) have provided some information on CB-M1 communication. In particular, inhibitory interactions between CB and M1 have been demonstrated using a paradigm called CB-brain inhibition (CBI). This involves applying a TMS pulse over the CB at specific intervals (5–7 ms) prior to a second stimulus over contralateral M1, producing a motor evoked potential (MEP) that is reduced in amplitude relative to an MEP produced by M1 stimulation alone [5–7]. CBI is thought to involve activation of purkinje cells in CB cortex, leading to inhibition of the dentate nucleus and consequent disfacilitation of M1 via projections through the motor thalamus (for review, see; [8]). Activity of this pathway is known to be modified during the learning of adaptation tasks that rely heavily on input from the CB [9–11], with larger changes in CBI predicting better performance [11]. Furthermore, manipulating activity in the CB-M1 pathway can influence neuroplasticity in M1 [12–14]. Consequently, CB-M1 connections are important for the acquisition of new motor skills, and CB-dependent changes in M1 neuroplasticity are one way by which CB may influence motor output.

While this literature demonstrates the capacity of CB to influence M1 plasticity in a functionally relevant way, it remains unclear how this influence is mediated. In particular, the circuits within M1 that are targeted by CB are unknown. Given that previous research using TMS has shown that the activity of specific intracortical motor circuits relates to the acquisition of different motor skills [15], identification of the M1 circuitry that is affected by CB projections may allow the targeted modification of skill acquisition. Interestingly, growing evidence suggests that late indirect (I) wave inputs on to corticospinal neurons, which represent important predictors of neuroplasticity and motor learning [15–17], may be specifically modified by changes in CB excitability. For example, application of transcranial direct current stimulation (tDCS; a NIBS paradigm that induces neuroplastic changes in brain excitability) over CB specifically modulates paired-pulse TMS measures of late I-wave excitability [18]. In addition, the effects of CB tDCS on single-pulse TMS measures of M1 excitability are only apparent when stimulation is applied with an anterior-posterior current, which specifically activates late I-wave circuits [19]. Also, changes in late I-wave circuits following motor training were observed following a CB-dependent motor task, but were absent following a task with minimal CB involvement [15].

Based on this previous literature, it appears likely that CB projections to M1 influence activity within the late I-wave circuitry. However, the nature of this influence, particularly in relation to the plasticity of these circuits, remains unclear. The aim of this exploratory study is therefore to assess how changes in CB activity influence the excitability and plasticity of I-wave generating circuits in M1. To achieve this, CB excitability will be downregulated using cathodal tDCS, whereas plasticity targeting the early and late I-wave circuits will be concurrently induced using I-wave periodicity TMS (iTMS;[20, 21]).

## Methods

### Sample size and participants

While the effects of CB tDCS on iTMS have not been previously investigated, the study by Ates and colleagues [18] investigated the influence of CB tDCS on the excitability of the I-wave generating circuits. Consequently, sample size calculations based on this study are sufficient to demonstrate the effects of activation within the pathway of interest (i.e., cerebellar projections to I-wave circuits of M1). Examination of the findings reported by Ates and colleagues revealed that changes in short-interval intracortical facilitation (SICF; paired-pulse TMS protocol indexing I-wave excitability; [22, 23]) due to CB tDCS had an effect size of 0.67. Based on the results of an *a priori* power analysis utilising this effect size, with α = 0.05 and 1-β = 0.9, we will therefore recruit 21 individuals (half female) to participate in the proposed experiment.

All participants will be recruited via advertisements placed on notice boards within the University of Adelaide, in addition to on social media platforms. Exclusion criteria will include a history of psychiatric or neurological disease, current use of medications that effect the central nervous system, or left handedness. Suitability to receive TMS will be assessed using a standard screening questionnaire [24]. The experiment will be conducted in accordance with the Declaration of Helsinki, and has been approved by the University of Adelaide Human Research Ethics Committee (approval H-2019-252). Written, informed consent will be provided prior to participation. Upon completion of the study, all data will be made fully available via hosting on the open science framework repository (https://www.cos.io/osf).

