### Experimental arrangement

All participants will attend the laboratory for three separate sessions, with a washout period of at least 1 week between sessions. While the experimental protocol applied within each session will be the same, the ISI used for iTMS will vary between sessions (see below & Fig 1). Furthermore, the order in which each iTMS interval is applied will be randomised between participants. As diurnal variations in cortisol can influence the neuroplastic response to TMS, all plasticity interventions will be applied after 11 am and at approximately the same time of day within each participant.

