#### Cerebellar transcranial direct current stimulation (tDCS_CB_)

A Soterix Medical 1 x 1 DC stimulator (Soterix Medical, New York, NY) will be used to apply tDCS to CB. Current will be applied through saline-soaked sponge electrodes (EASYpads, 5 x 7 cm), with the cathode positioned over the same location used for CB TMS (i.e., 3 cm lateral and 1 cm inferior to inion, contralateral to M1 TMS) and anode positioned on the skin above the right Buccinator muscle [4, 13, 37]. Stimulation will be applied at an intensity of 2 mA for 15 mins [4, 13, 37], coincident with the application of iTMS to M1. Onset and offset of stimulation will be ramped over a 30 s period prior to and following iTMS application.

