### Statistical analysis

Kolmogorov-Smirnov tests will be applied to assess data distribution prior to statistical analysis, with log transformation applied when deviations from normal are indicated. Given that all data of interest will involve repeated-measures, linear mixed-model analysis with repeated-measures (LMM_*RM*_) will be used to perform all statistical comparisons. Each model will include single trial data, and previously reported methods [38] will be used to justify inclusion of random participant intercepts and/or slopes, and to optimize and assess model fit. To ensure measures are comparable between sessions, effects of iTMS session (iTMS_*1*.*5*_, iTMS_*4*.*5*_ & iTMS_*Sham*_) on baseline measures of MEP_*1mv*_, MEP_*PA*_, MEP_*AP*_ and CBI, in addition to responses recorded at the start of the iTMS intervention, will be investigated using one-factor LMM_*RM*_, with each measurement investigated in a separate model. Furthermore, effects of iTMS session and ISI (1.5 & 4.5 ms) on baseline SICF will be assessed using two-factor LMM_*RM*_.

Changes in excitability during the intervention will be assessed by comparing values averaged over the first, middle and last 12 stimuli of the iTMS block between iTMS sessions. Changes in corticospinal excitability following the intervention will be investigated by assessing the effects of iTMS session and time (Post 5, Post 30) on baseline-normalised MEP_*1mV*_ values. Changes in coil-orientation dependent measures of I-wave excitability following the intervention will be investigated by assessing effects of iTMS session, time and coil orientation (MEP_*PA*_, MEP_*AP*_) on baseline-normalised values. Changes in SICF measures of I-wave excitability following the intervention will be investigated by assessing effects of iTMS session, time and ISI on baseline-normalised values. Changes in CBI following the intervention will be investigated by assessing the effects of iTMS session and time on baseline-normalised CBI values. For all models, investigation of main effects and interactions will be performed using custom contrasts with Bonferroni correction, and significance will be set at *P* < 0.05. Data for all models will be presented as the estimated marginal means, whereas pairwise comparisons will be presented as the estimated mean difference (EMD) and 95% confidence interval (95%CI) for the estimate, providing a non-standardised measure of effect size.

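### The 90% power claim for 21 participants rests on an effect of cerebellar tDCS that no listed analysis tests, and it would not carry over to two-sided or Bonferroni-corrected session contrasts

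*Protocol article*

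**What the plan says.** Under Sample size and participants, the article acknowledges that the effect of cerebellar tDCS on iTMS has not been studied. It borrows from a study of cerebellar tDCS and I-wave excitability, in which changes in SICF "due to CB tDCS had an effect size of 0.67". It states that a calculation on this basis is enough to show effects in the cerebellum-to-M1 pathway, and continues: "with α = 0.05 and 1-β = 0.9, we will therefore recruit 21 individuals (half female) to participate in the proposed experiment". No test, sidedness or effect-size metric is given.

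The design is described under Experimental arrangement: "While the experimental protocol applied within each session will be the same, the ISI used for iTMS will vary between sessions". The three sessions use iTMS at 1.5 ms, iTMS at 4.5 ms and sham iTMS. On tDCS the article says: "Stimulation will be applied at an intensity of 2 mA for 15 mins [4, 13, 37], coincident with the application of iTMS to M1". No sham-tDCS or no-tDCS session is described.

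Change in SICF is the primary outcome (section on I-wave excitability). Under Statistical analysis, it is analysed by a linear mixed model on single-trial data, testing iTMS session, time (Post 5, Post 30) and ISI on baseline-normalised values. Follow-up of main effects and interactions "will be performed using custom contrasts with Bonferroni correction", at P < 0.05, and pairwise differences are reported with 95% confidence intervals.

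**The concern.** A power statement has meaning only for a named comparison. Here the effect size describes what tDCS does to SICF, while the factor that varies between sessions is the iTMS interval. The number that justifies the sample size is thus attached to a comparison that the listed analyses do not make.

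There is a second difficulty. The listed inference uses Bonferroni-corrected contrasts and 95% confidence intervals, and mentions no directional test. A sample size of 21 at 0.67 looks too small for 90% power under that kind of inference.

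What is at stake is the reading of the primary result. The 90% figure is the only justification offered for the sample size. A finding of no difference in SICF between sessions could be read as coming from a study with a 10% risk of missing the effect, and the article does not support that reading for the tests it lists.

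**Working it through.** **Step 1. Set the effect size beside the analysis.**

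| | Sample-size section | Design and listed SICF analysis |
|---|---|---|
| What produces the effect | Cerebellar tDCS | iTMS interval (1.5 ms, 4.5 ms, sham) |
| Does tDCS vary? | Yes, it is the cause of the effect | No, it is the same in every session |
| Terms tested | Not stated | iTMS session, time, ISI |
| Multiplicity | None mentioned; α = 0.05 | Bonferroni-corrected contrasts |

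No listed test compares tDCS with no tDCS, and none compares SICF with its baseline value. This step needs no arithmetic.

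**Step 2. Inputs for the numerical check.**

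- From the article: effect size 0.67, α = 0.05, power 0.90, n = 21, all participants attending all three sessions.
- Assumed: 0.67 is a paired dz for one session contrast, with one value per participant.
- Inferred: two-sided testing, from the 95% confidence intervals.
- Assumed: two or three contrasts in the Bonferroni family. The article gives no number; three is the count of pairwise comparisons among three sessions.

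**Step 3. Formula.** For a paired t test, df = n − 1 and the noncentrality is δ = dz × √n. Power is the probability that a noncentral t with these parameters exceeds the critical value. At n = 21, δ = 0.67 × √21 = 3.070 and df = 20.

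**Step 4. Reproduce the stated 21.** One-sided, α = 0.05: the critical t is 1.725 and power is 90.6%. With n = 20 it is 89.3%, so 21 is exactly the one-sided minimum.

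**Step 5. The same n under other inferences (dz = 0.67).**

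| Test | α per contrast | Critical t (df 20) | Power at n = 21 | n for 90% |
|---|---|---|---|---|
| One-sided | 0.05 | 1.725 | 90.6% | 21 |
| Two-sided, uncorrected | 0.05 | 2.086 | 83.1% | 26 |
| Two-sided, Bonferroni for 2 | 0.025 | 2.423 | 73.7% | 31 |
| Two-sided, Bonferroni for 3 | 0.0167 | 2.613 | 67.5% | 34 |

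**Step 6. Another route to 21.** Take a repeated-measures ANOVA F test over m = 3 sessions, with 0.67 halved to f = 0.335 and a correlation of ρ = 0.5. Then λ = f² × n × m / (1 − ρ) = 0.1122 × 21 × 3 / 0.5 = 14.14, with 2 and 40 degrees of freedom. Power is 91.0% at n = 21 and 89.4% at n = 20, so this also gives 21. It needs a halving and a correlation that the article does not state, and it powers an omnibus test rather than the corrected contrasts. With f = 0.67 over three sessions the answer would be 7 (ρ = 0.5) or 11 (ρ = 0).

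**Step 7. Detectable effect at n = 21, two-sided.** Uncorrected, 90% power is reached at dz = 0.744 (0.74 gives 89.7%), so about 0.75. Corrected for three contrasts, dz = 0.87 gives 90.3%.

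**The case against.** A reader might infer that the authors ran a one-sided test and so made an arithmetic error. The article does not support this. It states no test or sidedness, and Step 6 shows a non-directional route to the same 21 that fits a three-session within-participant design. The meaning of 0.67 also depends on a cited study that is not at hand.

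A reader might also take 83% or 68% as the true power of the trial. That goes too far as well. If 0.67 does not describe a session contrast, figures computed from it are no firmer than the 90%. The planned analysis is a mixed model on single trials, whose power cannot be computed from this article in either direction. Two-sidedness is inferred, the number of contrasts is assumed, and 83% applies before any correction.

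Nor should one say that the design holds nothing related to the borrowed effect. SICF is recorded before and after the intervention in the sham-iTMS session, which also receives tDCS. A pre-to-post change can be observed there, though without a tDCS control and not as a listed test.

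Finally, the authors call the study exploratory, disclose that the effect was borrowed and say why; and a condensed article may leave the details of a power calculation to a fuller document. These points stand, and the missing detail alone would be no finding. They do not remove the mismatch. The article itself fixes the source of the effect, the constant tDCS and the listed tests, and it presents a formal a priori power analysis as sufficient. Absence of earlier data explains the borrowing but does not turn a tDCS effect into an iTMS-interval effect. The ANOVA route does not help either, because it does not power the corrected contrasts.

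**Conclusion.** The point holds in this form: the 90% power attaches to no listed analysis, because 0.67 is an effect of cerebellar tDCS and tDCS is constant across sessions. This part rests on the article's text alone.

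The size of the shortfall is conditional. If 0.67 is taken as a paired dz for one session contrast, on participant means and two-sided, then 21 participants give 83.1% power uncorrected, 73.7% with Bonferroni for two contrasts and 67.5% for three. More contrasts would lower it further. A one-sided origin of the 21 is possible but not shown, and the power of the planned mixed model remains unknown.

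**What to change.** Keep 21 participants and rewrite the sample-size paragraph:

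- Name the primary SICF contrast, the test, its sidedness, the effect metric and the number of contrasts in the Bonferroni family.
- Withdraw the statement that the calculation is enough to demonstrate the pathway effect, or label 0.67 as an assumed effect for an iTMS contrast.
- Replace the 90% claim with a sensitivity statement. For example: with 21 participants, a two-sided paired contrast has 90% power for dz of about 0.75 (about 0.87 if Bonferroni-corrected for three contrasts); at an assumed dz of 0.67, power is about 83% uncorrected and 68% corrected for three. If the named family has a different number of contrasts, recompute the corrected figures.
- Say that these figures refer to a paired t test on participant means and only approximate the mixed model.

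The cost is one paragraph and a less favourable stated power. The design, the number of participants and the analysis model do not change.

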### Experimental arrangement

All participants will attend the laboratory for three separate sessions, with a washout period of at least 1 week between sessions. While the experimental protocol applied within each session will be the same, the ISI used for iTMS will vary between sessions (see below & Fig 1). Furthermore, the order in which each iTMS interval is applied will be randomised between participants. As diurnal variations in cortisol can influence the neuroplastic response to TMS, all plasticity interventions will be applied after 11 am and at approximately the same time of day within each participant.

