#### I-wave periodicity repetitive TMS (iTMS)

In accordance with previous literature [21, 35], iTMS will consist of 180 pairs of stimuli applied every 5 s, resulting in a total intervention time of 15 mins. The same intensity will be used for both stimuli, adjusted to produce a response of ~ 1mV when applied as a pair. These stimuli will be applied using ISI’s of 1.5 (iTMS_*Early*_) and 4.5 ms (iTMS_*Late*_) in separate sessions. These parameters produce robust potentiation of MEP amplitude [20, 21, 35, 36]. A sham stimulation condition (iTMS_*Sham*_) that is not expected to modulate corticospinal excitability will also be applied in a third session. Within this condition, we will stimulate intervals that correspond to the transition between the peaks and troughs of facilitation that are observed within a complete SICF curve, as these are not expected to induce any changes in excitability. This will include equal repetitions of 1.8, 2.3, 3.3, 3.8 and 4.7 ms ISI’s, applied randomly and with an inter-trial jitter of 10%.

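### Cathodal cerebellar tDCS is the same in all three sessions, so the effect of cerebellar modulation on iTMS-induced I-wave plasticity, the stated aim, is not identified at any sample size

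*Protocol article*

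**What the plan says.** The Introduction gives the aim as to "assess how changes in CB activity influence the excitability and plasticity of I-wave generating circuits in M1" and the means as "CB excitability will be downregulated using cathodal tDCS", with iTMS inducing plasticity at the same time. The I-wave excitability section repeats that cerebellar modulation is the main interest and makes SICF the primary outcome.

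The design is in Experimental arrangement: "All participants will attend the laboratory for three separate sessions, with a washout period of at least 1 week between sessions". On what differs between sessions it says "While the experimental protocol applied within each session will be the same, the ISI used for iTMS will vary between sessions", and on randomisation, "the order in which each iTMS interval is applied will be randomised between participants".

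The iTMS section gives two active intervals, 1.5 ms and 4.5 ms, in separate sessions, and a sham iTMS condition in the third. The tDCS section describes one cathodal setting, delivered "coincident with the application of iTMS to M1". No sham, anodal or absent tDCS condition is described. Fig 1 is not available, but its caption lists a single tDCS term.

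The models in Statistical analysis use iTMS session, time and, depending on the outcome, SICF interval or coil orientation. None has a tDCS term. That section also plans to regress CBI change against changes in corticospinal and intracortical measures.

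Sample size and participants takes an effect size of 0.67 for the SICF change caused by cerebellar tDCS in an earlier study, and states that "sample size calculations based on this study are sufficient to demonstrate the effects of activation within the pathway of interest".

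**The concern.** The research question is about cerebellar state, and cerebellar state is the one thing the design holds fixed. A comparison of iTMS sessions made entirely under cathodal tDCS cannot show whether the tDCS made the iTMS response larger, smaller or left it alone.

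The interpretation of the main result depends on this. If iTMS shows no effect, the data cannot separate tDCS having blocked it from iTMS having failed in this sample. If iTMS shows an effect, they cannot separate tDCS being irrelevant from tDCS having altered its size. Both outcomes could be written up as findings about the cerebellum, and neither would be one. The gap cannot be repaired once data collection is over.

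**Working it through.** **1. The plan's own figure.** Inputs from Sample size and participants: d = 0.67, α = 0.05, power 0.90, N = 21. Treat d as a paired standardised difference (an assumption; the test is not named). The noncentrality is d√n = 0.67 × √21 = 3.07. A one-sided paired t-test then has power 0.906 at n = 21, and 21 is the smallest n reaching 0.90, so the figure reproduces. A two-sided test has power 0.831 at 21 and needs 26. Sidedness is a separate matter. What counts here is that d describes SICF change caused by tDCS, which would have to be tested with tDCS on against tDCS off or sham.

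**2. What the sessions estimate.** Let T = 1 with cathodal tDCS and T = 0 without. Write the mean baseline-normalised response in a session with iTMS condition i as

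m + a_i + t·T + g_i·T, with a = g = 0 for sham iTMS.

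- m: no change (100%) plus drift with time, repeated testing and any effect of the control intervals
- a_E, a_L: effects of early and late iTMS without tDCS
- t: direct effect of tDCS (the excitability half of the aim)
- g_E, g_L: change in the iTMS effect caused by tDCS (the plasticity half)

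All three planned sessions have T = 1:

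| Session | Mean |
|---|---|
| Sham iTMS | m + t |
| Early, 1.5 ms | m + a_E + t + g_E |
| Late, 4.5 ms | m + a_L + t + g_L |

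The contrasts are:

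- Early − Sham = a_E + g_E
- Late − Sham = a_L + g_L
- Early − Late = (a_E − a_L) + (g_E − g_L)

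Each g appears only added to its a. Any value of g_E fits the same data if a_E is shifted to match. The early-late contrast isolates a cerebellar effect only if a_E = a_L, which the study does not test.

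**3. Rank check.** With columns [1, Early, Late, tDCS, Early × tDCS, Late × tDCS], the three planned sessions give rank 3 of 6. Adding a sham-tDCS counterpart to each iTMS condition (3 × 2 = 6 cells) gives rank 6. Time, SICF interval and coil orientation are crossed within session, so the same aliasing recurs at every level of them. N does not enter the argument.

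**4. The excitability half.** The sham iTMS session estimates m + t. This equals a tDCS effect only if m is exactly 100%: no drift, no retest effect and inert control intervals. The plan expects the control intervals to be inert, but nothing controls for drift or retesting.

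**5. Would moving one visit to sham tDCS be enough?** Late with tDCS minus Late without tDCS = t + g_L, so the direct effect and the change in plasticity stay mixed. If the sham iTMS session is also kept, there are three means for four unknowns (m, a_L, t, g_L). Isolating g_L needs four cells: (Late on − Late off) − (Sham on − Sham off) = (t + g_L) − t = g_L. Both intervals need six.

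**The case against.** The strongest defence is that the plan is not silent on the cerebellum.

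- The sham iTMS session is close to tDCS alone, and its pre-post change bears on excitability.
- CBI is measured at baseline, 5 minutes and 30 minutes and is modelled, which gives some check that the cerebellar pathway moved.
- The CBI regression is meant to link that movement to plasticity.
- The iTMS section cites earlier work in which both active intervals raised responses, which could serve as a benchmark.
- The study calls itself exploratory.

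Much of this stands as a limit on how far the criticism goes. A reader might infer that the study carries no information at all about cerebellar influence. The documents do not support that: the first three items are evidence, though the first two are uncontrolled and the regression is correlational, because CBI change is not randomised and is measured after tDCS and iTMS together. Nor are the iTMS comparisons invalid. The order of intervals is randomised, and the effect of iTMS during cathodal tDCS is properly estimable.

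None of it supplies the missing comparator for plasticity. No comparison with historical iTMS data is planned, and the sample size section itself says that the effect of cerebellar tDCS on iTMS has not been studied before. The exploratory label affects how firmly results are claimed, not which effects can be estimated.

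A reader might also infer that turning one of the three visits into a sham-tDCS visit would cure the problem. Step 5 of the working shows that it would not.

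**Conclusion.** The point holds for the plasticity half of the aim. The effect of cerebellar modulation on iTMS-induced I-wave plasticity is fully aliased with the effect of iTMS itself (rank 3 of 6), whatever the sample size and whatever an analysis plan might add. For the excitability half there is a weak estimate, confounded with time, repeated testing and any effect of the control intervals. The statement that N = 21 suffices to demonstrate the cerebellar pathway's effect is unsupported, because no planned contrast corresponds to the effect size of 0.67.

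This rests on reading the text as giving the same cathodal tDCS in every session. The text says so directly, and the caption of the missing figure does not suggest otherwise. It does not rest on the sidedness behind N = 21, nor on any assumed effect size. It should be settled before the study reports, because it determines what the study may conclude.

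**What to change.** Change the text:

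- Restate the aim, and limit the conclusions, to the effects of iTMS at 1.5 ms, 4.5 ms and the control intervals, all delivered during cathodal cerebellar tDCS.
- State that attribution of those effects to the cerebellum is not identified.
- Describe the sham iTMS pre-post change and the CBI change as uncontrolled, and the CBI regression as correlational.
- Remove the statement that N = 21 is sufficient to demonstrate the effect of the cerebellar pathway.

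This costs wording only. The downside is a narrower claim.

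Keeping the full plasticity claim is not cheap. Active versus sham tDCS would have to be a randomised within-participant factor, with sham-tDCS counterparts for at least one active and one control iTMS condition. That is four cells, or six for both intervals, against three visits now. The models would need tDCS and iTMS × tDCS terms, and the study should be sized on that interaction. The documents give no effect size for it. As an illustration at 90% power (paired t, one-sided / two-sided):

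| Assumed standardised contrast | N |
|---|---|
| 0.67 | 21 / 26 |
| 0.67/√2 = 0.47 | 40 / 49 |
| 0.67/2 = 0.335 | 78 / 96 |

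All three rows are assumptions about the interaction. Re-allocating a single existing visit would need an ethics amendment, lose a current condition and still leave the interaction unidentified.
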